#### *Contrasts between study arms (unpaired design)*

Analyses will compare the difference in detection probabilities (DPs) between study arms. The DP is the probability of being endpoint-positive given the study arm and, possibly, either or both screening tests being positive. For example the DP of ISUP1 in men randomised to the experimental arm and Stockholm3-positive is equal to  $\Pr(\text{ISUP1} \mid \text{Stockholm3} \geq 11\%, \text{Experimental arm})$ .

**Absolute scale.** The absolute difference in DPs is defined as the DP in the experimental arm minus the DP in the standard arm ( $\Delta\text{DP} = \text{DP}_{\text{Exp}} - \text{DP}_{\text{Std}}$ ) or vice versa, as appropriate. It is estimated by plugging into the formula the observed proportions. An approximate 100(1- $\alpha$ )% two-sided Wald confidence interval for  $\Delta\text{DP}$  is calculated as

$$\widehat{\Delta\text{DP}} \pm z_{\alpha/2} \sqrt{\frac{\widehat{\text{DP}}_{\text{Exp}}(1-\widehat{\text{DP}}_{\text{Exp}})}{n_{\text{Exp}}} + \frac{\widehat{\text{DP}}_{\text{Std}}(1-\widehat{\text{DP}}_{\text{Std}})}{n_{\text{Std}}}}.$$

**Relative scale.** The relative difference in DPs is defined as the DP in the experimental arm divided by the DP in the standard arm ( $r\text{DP} = \text{DP}_{\text{Exp}}/\text{DP}_{\text{Std}}$ ) or vice versa, as appropriate. It is estimated by plugging into the formula the observed proportions. An approximate 100(1- $\alpha$ )% two-sided Wald confidence interval for  $r\text{DP}$  is calculated as

$$\exp\left(\log(\widehat{r\text{DP}}) \pm z_{\alpha/2} \sqrt{\frac{1}{\widehat{\text{DP}}_{\text{Exp}} * n_{\text{Exp}}} - \frac{1}{n_{\text{Exp}}} + \frac{1}{\widehat{\text{DP}}_{\text{Std}} * n_{\text{Std}}} - \frac{1}{n_{\text{Std}}}}\right).$$

Contrasts 3 vs 1, 2 vs 1, and 9 vs 7 will be analysed using absolute differences (Study 1). Contrasts 6 vs 1, and 5 vs 1 will be analysed using relative differences (Study 2).

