#### *Interpretation as relative sensitivity*

It should be noted that rDPs can (under the assumption of no false positive biopsies, see SAP Appendix 1) be interpreted as relative true positive fractions (rTPF) (ie, relative sensitivities).

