### Primary endpoints

Contrasts between study arms: we will assess the non-inferiority of the experimental arm versus the standard arm in detecting ISUP $\geq 2$  cancers ( $\delta = 0.04$  or  $\exp(-\delta) = 0.78$ , as appropriate). The  $\alpha$  level is set to 0.025. Two-sided 95% confidence intervals will be reported.

Contrasts within study arms: we will assess the non-inferiority of the Stockholm3 test versus PSA in detecting ISUP $\geq 2$  cancers ( $\exp(-\delta) = 0.78$ ) and the superiority of PSA versus the Stockholm3 test in detecting ISUP1 cancers (i.e. a lower proportion of ISUP1 cancer detected according to the Stockholm3 test) ( $\exp(-\theta) = 1$ ). The  $\alpha$  level is set to 0.025 for both tests. Two-sided 95% confidence intervals will be reported.

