### Additional analyses

Due to updates in the Stockholm3 assay system to reduce measurement errors in the biomarkers included in the Stockholm3 risk prediction model, Stockholm3  $\geq 11\%$  as a selection criterion for randomization may be more sensitive than PSA  $\geq 3$  (i.e. more men with clinically significant prostate cancer will be randomized based on the criterion Stockholm3  $\geq 11\%$  compared with PSA  $\geq 3$ ). If this turns out to be true, we will perform analyses where we “count backwards” (increase the S3M cutoff) and compare biopsy rates at identical sensitivity for clinically significant prostate cancer when comparing diagnostic strategies involving S3M compared with PSA  $\geq 3$  (as described in Grönberg et al.).

We will artificially randomise (2:3) those men who screened negative on both screening tests. By doing this, the totals [d]+[h] and [d']+[h'] will become known, which in turn will allow the estimation of quantities like  $\Pr(\text{ISUP} \geq 2, \text{Stockholm3} \geq 11\% \mid \text{Standard arm})$  (i.e., the probability of ISUP  $\geq 2$  and Stockholm3  $\geq 11\%$  in enrolled men randomised to the standard arm). Contrasts between the two study arms with respect to these quantities will be

---

 Where applicable.

performed using the same methodology described in the section “Contrasts between study arms (unpaired design)”.

We may in additional analyses use regression models to model the DP, TPF, and FPF given covariates. We will employ standard generalised linear models or marginal models (Pepe and Alonzo 2001), as appropriate.

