## Post-hoc analyses

Ignoring biopsy results on men with negative MRI and Stockholm3  $\geq 25\%$

In order to estimate results in the counterfactual scenario where participants with negative MRI and Stockholm3  $\geq 25\%$  would not have been referred to undergo systematic biopsy, we will perform analyses where these biopsies are ignored. To be clear, we will not exclude these men from the analyses, but ignore their biopsy and biopsy outcome (i.e., they would enter the analyses as not having had a biopsy or any potential cancer diagnosis). The participants with a negative MRI and Stockholm3  $\geq 25\%$  will in these analyses thus contribute to the counts of performed MRI scans, but not to the count of biopsies or the cancer count. Apart from this, the analyses will be performed identically as detailed above.

## Appendix 1

Let  $T$  and  $S$  be the events “SBx+TBx positive for a specific ISUP grade” (eg, ISUP $\geq 2$ ) and “SBx positive for a specific ISUP grade”, respectively. Let  $P$  be the event “PSA screening test above 3 ng/ml”. Let  $D$  be the event “the subject is positive for a specific ISUP grade (true, unobservable status)”.

The main between-arm contrast of Study 1, expressed in relative terms, is given by

$$\frac{\Pr(T = 1|P = 1)}{\Pr(S = 1|P = 1)}.$$

This can be rewritten as:

$$\begin{aligned} \frac{\Pr(T = 1|P = 1)}{\Pr(S = 1|P = 1)} &= \frac{\Pr(T = 1, D = 1|P = 1) + \Pr(T = 1, D = 0|P = 1)}{\Pr(S = 1, D = 1|P = 1) + \Pr(S = 1, D = 0|P = 1)} \\ &= \frac{\Pr(T = 1, D = 1|P = 1) + \Pr(T = 1|D = 0, P = 1)\Pr(D = 0|P = 1)}{\Pr(S = 1, D = 1|P = 1) + \Pr(S = 1|D = 0, P = 1)\Pr(D = 0|P = 1)} \quad [\text{assumption}] \\ &= \frac{\Pr(T = 1|D = 1, P = 1)\Pr(D = 1|P = 1)}{\Pr(S = 1|D = 1, P = 1)\Pr(D = 1|P = 1)} = \frac{\Pr(T = 1|D = 1, P = 1)}{\Pr(S = 1|D = 1, P = 1)} = r_{TPF} \end{aligned}$$

The third equality holds under the assumption that the FPFs  $\Pr(T = 1|D = 0, P = 1)$  and  $\Pr(S = 1|D = 0, P = 1)$  are equal to zero, while the fourth equality hinges on the fact that — because of randomisation — the probabilities  $\Pr(D = 1|P = 1)$  in the two study arms are the same in expectation.

The equation above can be extended to the other between-arm contrasts.

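### The SAP writes no formula for the primary between-arm ratio (Strategy 6 vs 1, and 5 vs 1), and its detection probability, followed as defined and illustrated, does not give the relative sensitivity it claims

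*Combined protocol and SAP*

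**What the plan says.** The SAP section *Contrasts between study arms (unpaired design)* defines the quantity compared: "The DP is the probability of being endpoint-positive given the study arm and, possibly, either or both screening tests being positive". One example follows: "For example the DP of ISUP1 in men randomised to the experimental arm and Stockholm3-positive is equal to" the probability of ISUP 1 conditional on Stockholm3 ≥11% and the experimental arm. Contrasts 3 vs 1, 2 vs 1 and 9 vs 7 are put on the absolute scale. For the rest: "Contrasts 6 vs 1, and 5 vs 1 will be analysed using relative differences (Study 2".

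The next section, *Interpretation as relative sensitivity*, says that ratios of DPs (rDP) can, if biopsies give no false positives, "be interpreted as relative true positive fractions (rTPF) (ie, relative sensitivities". Appendix 1 proves this with PSA ≥3 ng/ml as the condition in both arms, and ends: "The equation above can be extended to the other between-arm contrasts".

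Under *Primary endpoints*, the relative non-inferiority margin is 0.78 and the α "level is set to 0.025. Two-sided 95% confidence intervals will be reported".

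The joint form, Pr(ISUP ≥2 and test positive | arm), appears in two places. The note in *Contrasts within study arm (paired design)* prints it for the experimental arm and calls it a detection probability. *Additional analyses* plans it between arms, after this step: "We will artificially randomise (2:3) those men who screened negative on both screening tests".

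**The concern.** Contrast 6 vs 1 carries the overarching primary hypothesis and 5 vs 1 carries additional hypothesis 4. They are the only between-arm contrasts assigned to the relative scale, and the only ones listed there in which the two arms use different blood tests.

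In the between-arm definition, test positivity can enter only as a condition. Leaving the condition out gives Pr(endpoint | arm), which is 9 vs 7, not 6 vs 1. Following the definition for 6 vs 1 therefore leads to

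Pr(ISUP ≥2 | Stockholm3+, Exp) / Pr(ISUP ≥2 | PSA+, Std).

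Each term is the predictive value of the blood test multiplied by the sensitivity of the work-up. Appendix 1 works because randomisation equalises Pr(D=1 | PSA+) between arms. Randomisation does not equalise Pr(D=1 | Stockholm3+) with Pr(D=1 | PSA+), so that factor does not cancel. At stake is what the 0.78 margin measures in the trial's main claim, and whether two analysts working from this SAP would use the same denominators.

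**Working it through.** **Inputs.** From the SAP: 18% ISUP ≥2 among PSA ≥3 men on systematic biopsy; assumed ratio 1.25 for MRI-targeted against systematic biopsy; absolute margin 0.04; 303 PSA-positive men among 415 in the control arm and 623 in the MRI arm; 80% power; about 2100 randomised, of whom about 1600 have PSA ≥3; 20% drop-out; 2:3 allocation; margin 0.78; one-sided α 0.025. From protocol section 8.2: 32% of biopsies saved at equal sensitivity. The number of Stockholm3-positive men is not given and is treated as an assumption.

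**The plan's own figures.** The relative margin matches the absolute one: 1 − 0.04/0.18 = 0.778. For the 80% power I used Φ((margin + p2 − p1)/SE − 1.96) with unpooled SE. The SAP bootstrapped earlier trial data, so this is an approximation.

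- Joint scale, 415 vs 623 men: p1 = 0.18 × 303/415 = 0.131, p2 = 0.225 × 303/415 = 0.164, margin 0.04 × 303/415 = 0.029. Power 79.6%.
- Conditional scale, 303 vs 303 × 1.5 = 454.5 men: p1 = 0.18, p2 = 0.225, margin 0.04. Power 82.1%.

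The joint scale fits slightly better, but only because the margin is rescaled too; with 0.04 left unscaled it gives 90.5%. The power figure does not settle which form was meant.

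**Algebra.** Since Pr(T | S3+, Exp) = Pr(T, S3+ | Exp)/Pr(S3+), and likewise for PSA,

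conditional rDP = [Pr(T, S3+ | Exp)/Pr(S, PSA+ | Std)] × Pr(PSA+)/Pr(S3+).

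If no biopsy is falsely positive, the bracket equals [Pr(T, S3+ | D=1) × Pr(D=1)] / [Pr(S, PSA+ | D=1) × Pr(D=1)]. Here Pr(D=1) among randomised men does cancel by randomisation, leaving the relative sensitivity of the two pathways. The factor outside the bracket is the discrepancy.

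**Size.** The true relative sensitivity when the conditional rDP is 0.78 is 0.78 × (number S3+)/1600. The chance of claiming non-inferiority uses the SAP's log-ratio Wald SE, 2100 × 0.8 = 1680 completers split 672/1008, and an 18% control rate. Example, 1400 Stockholm3-positive: n = 512 and 672; DPs 0.18 and 0.78 × 0.18 × 1600/1400 = 0.160; SE 0.129; ln(1600/1400) = 0.134; 0.134/0.129 − 1.96 = −0.93, or 18%.

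| Stockholm3+ of 2100 | True relative sensitivity at conditional rDP 0.78 | Chance of claim, true value 0.78 | Chance of claim, true value 1.25 |
|---|---|---|---|
| 500 (fewest possible) | 0.24 | about 100% | about 100% |
| 1088 (0.68 × 1600) | 0.53 | 86% | about 100% |
| 1400 | 0.68 | 18% | about 100% |
| 1600 | 0.78 | 2.5% | 98% |
| 1800 | 0.88 | 0.2% | 86% |
| 2100 (all) | 1.02 | <0.1% | 40% |

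The joint ratio gives 2.5% in the third column and 98% in the fourth, whatever the count.

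**The case against.** The SAP never writes the conditional ratio for 6 vs 1. The definition says that test positivity is only possibly a condition, and the single example concerns ISUP 1 in one arm. Where the SAP does print a ratio comparing two different blood tests, in the within-arm note, it uses the joint form and calls it a ratio of detection probabilities. The protocol's primary aim and the SAP's hypotheses speak of numbers of cancers and biopsies, not yield per test-positive man. Putting only the different-test contrasts on the relative scale also makes sense if the joint form was meant, because a joint ratio does not need the unknown number of men negative on both tests. Under the joint reading, the extension in Appendix 1 holds and is merely not shown.

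All of this makes a joint intention plausible. It does not supply the missing formula, and *Additional analyses* treats the joint between-arm contrast as something separate from the main one.

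Three stronger inferences are tempting and go too far:

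- That the SAP has fixed a wrong estimand. It has left the estimand unwritten, with an unsuitable illustration.
- That the effective margin is 0.53, so that missed cancers would pass as non-inferior. This carries over a 32% saving from an earlier study. It would leave 2100 − 1088 = 1012 Stockholm3-negative men, all necessarily PSA-positive, or 63% of 1600. *Additional analyses* expects that Stockholm3 ≥11% may prove more sensitive than PSA, and a count above 1600 would make the test too strict.
- That the biopsy saving would be understated by a known amount. *Key secondary endpoints* gives no biopsy formula, and a simple figure would leave out MRI-negative men with Stockholm3 ≥25%, who are biopsied.

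**Conclusion.** The point holds as a defect of specification in the primary between-arm analysis. Followed as defined and illustrated, the rDP for 6 vs 1 and 5 vs 1 is relative sensitivity times the ratio of PSA-positive to Stockholm3-positive men. The stated interpretation and the Appendix 1 extension then fail for exactly the contrasts placed on the relative scale. The two agree only if both tests flag the same number of men.

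The algebra needs only the SAP's own assumption of no false-positive biopsies. The size and direction depend on a Stockholm3-positive count that the documents do not give; the claim probabilities also assume an 18% control rate, 1680 completers and a normal approximation. The documents do not show that the sponsor meant the conditional form, nor that any bias would favour the experimental pathway. Contrasts 3 vs 1, 2 vs 1 and 9 vs 7 are unaffected, because each applies the same screening criterion in both arms.

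**What to change.** In *Contrasts between study arms*, state the primary rDP for 6 vs 1 and 5 vs 1 (ISUP ≥2, ISUP 1 and biopsies) as

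[(a'+b')/n_Exp] / [(a+c)/n_Std],

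where n_Exp and n_Std are all men of the analysis population (ITT or PP) randomised to each arm, whichever test made them eligible. The existing Wald interval applies with these proportions, and the 0.78 margin then refers to relative sensitivity.

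In Appendix 1, limit the conditional proof to contrasts that use the same screening criterion in both arms. Add the joint derivation, in which Pr(D=1) among randomised men cancels, and adjust *Interpretation as relative sensitivity* to match.

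The artificial randomisation is not needed for this ratio: all screen-positive men were randomised 2:3, so in expectation the ratio over randomised men equals that over enrolled men. It may stay for absolute probabilities in enrolled men.

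The cost is SAP wording only, with the same data and interval formula.

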#### *Interpretation as relative sensitivity*

It should be noted that rDPs can (under the assumption of no false positive biopsies, see SAP Appendix 1) be interpreted as relative true positive fractions (rTPF) (ie, relative sensitivities).

#### *Contrasts within study arm (paired design)*

Analyses will compare the true positive fraction between Stockholm3 and PSA, within either study arm. Comparisons will be made on a relative scale. rTPF is defined as  $TPF_{\text{Stockholm3}}/TPF_{\text{PSA}}$  or vice versa, as appropriate.

The rTPF (standard arm) is estimated as  $(a+b)/(a+c)$  (or  $(a+c)/(a+b)$ , as appropriate) and an approximate  $100(1-\alpha)\%$  two-sided confidence interval for rTPF is calculated as

$$\exp\left(\log(\widehat{rTPF}) \pm z_{\alpha/2} \sqrt{\frac{b+c}{(a+b)(a+c)}}\right).$$

Analogous formulas are used for comparisons within the experimental arm and for the relative False Positive Fraction.

Note: the quantity  $(a+b)/(a+c)$  estimates the rTPF in both the enrolled and randomised population. It also estimates the ratio of detection probabilities like  $\Pr(\text{ISUP} \geq 2, \text{Stockholm} \geq 11\% \mid \text{Experimental arm}) / \Pr(\text{ISUP} \geq 2, \text{PSA} \geq 3 \text{ ng/ml} \mid \text{Experimental arm})$ .

#### *Non-inferiority and superiority tests*

The null and the alternative hypothesis for a non-inferiority test for the  $\Delta DP$  are:

$$\begin{aligned} H_0: \Delta DP &\leq -\delta \\ H_a: \Delta DP &> -\delta \end{aligned}$$

where  $\delta > 0$  is the non-inferiority margin. This means that non-inferiority for a specific endpoint will be claimed if the lower boundary of the two-sided  $(2\alpha \times 100)\%$  confidence interval for the  $\Delta DP$  does not cover  $-\delta$ .

The null and the alternative hypothesis for a superiority test for the  $\Delta DP$  are:

$$\begin{aligned} H_0: \Delta DP &\leq \theta \\ H_a: \Delta DP &> \theta \end{aligned}$$

where  $\theta \geq 0$  is the superiority margin. This means that superiority for a specific endpoint will be claimed if the lower boundary of the two-sided  $(2\alpha \times 100)\%$  confidence interval for the  $\Delta DP$  does not cover  $\theta$ .

For comparisons on a relative scale (rTPF), the null and the alternative hypothesis for non-inferiority and superiority tests are

$$H_0: rDP \leq \exp(-\delta)$$

$$H_a: rDP > \exp(-\delta)$$

and

$$\begin{aligned} H_0: rDP &\leq \exp(\theta) \\ H_a: rDP &> \exp(\theta) \end{aligned}$$

respectively, with non-inferiority and superiority margins equal to  $\delta > 0$  and  $\theta \geq 0$ .

One-sided p-values will be calculated based on the test considered (non-inferiority or superiority).

Switching from non-inferiority to superiority: if the two-sided  $(2(1 - \alpha) \times 100)\%$  confidence interval for  $\Delta DP$  (rTPF) not only lies entirely above the non-inferiority margin, but also above the superiority margin, superiority will be claimed at the same alpha-level set for the non-inferiority test. In this case, we will also calculate the p-value associated with a test for superiority.

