#### *Basic data and assumptions used in the sample size calculations*

We used data from the STHLM3 trial for sample size calculations. In this data, 18% of men with PSA  $\geq 3$  had a clinically significant prostate cancer when biopsied with SBx. We further

noted that  $rTPF=1.25$  for clinically significant prostate cancer comparing MRI+TBx with SBx based on the results from a meta-analysis (Schoots et al. 2015). We set the noninferiority delta to 4 percentage points for demonstrating noninferiority with respect to sensitivity of clinically significant prostate cancer. We set the alpha to 0.025.

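### The SAP's rules for claiming non-inferiority and superiority are written with confidence levels of 5% and 195%, and its interval formulas imply 97.5%, where 95% is evidently meant

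*Combined protocol and SAP*

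**What the plan says.** The claim rules are in the SAP section on non-inferiority and superiority tests.

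- **Non-inferiority on ΔDP:** the claim depends on whether the "lower boundary of the two-sided $(2\alpha \times 100)\%$ confidence interval" covers −δ.
- **Superiority on ΔDP:** "superiority for a specific endpoint will be claimed if the lower boundary of the two-sided" interval, with the same 2α level, does not cover θ.
- **Switching from non-inferiority to superiority, for ΔDP and rTPF:** the condition begins "if the two-sided $(2(1 - \alpha) \times 100)\%$ confidence interval" and requires that interval to lie above both margins.
- **Relative scale:** hypotheses are given for rDP, but no interval-based claim rule apart from the switching sentence.
- **P-values:** "One-sided p-values will be calculated based on the test considered (non-inferiority or superiority").

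The SAP sections on contrasts between arms (unpaired) and within arm (paired) define their intervals as two-sided 100(1−α)% with multiplier z_{α/2}.

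Under Primary endpoints the α "level is set to 0.025. Two-sided 95% confidence intervals will be reported". The key secondary endpoints have the same pair of statements. The note closing the sample size section gives each test a type I error of about 2.5%, and about 7% for three independent tests.

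**The concern.** This is the only section that says when non-inferiority or superiority will be claimed. None of the confidence levels written in it equals 95% at α = 0.025, and one exceeds 100%. The promise of 95% intervals elsewhere concerns what is reported and does not amend the claim rule.

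The interval formulas add a further level. An analyst who puts α = 0.025 into 100(1−α)% and z_{α/2} obtains a valid 97.5% interval and may see nothing amiss. Unlike 5% or 195%, that mistake could pass unnoticed. It would cost power, notably for Strategy 6 versus Strategy 3 within the experimental arm, where the SAP's own table already starts at 0.48.

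**Working it through.** **Inputs from the SAP.** One-sided α = 0.025. Margin 0.04 absolute or 0.78 relative. Stated type I error 2.5% per test, about 7% for three. Control detection rate 18%. rDP = 1.3 for Strategy 3 versus 1. About 1600 randomized men with PSA ≥ 3, and 20% drop-out. The 2:3 allocation is in the protocol and the SAP. Derived, not stated: 1600 × 0.8 = 1280 men, split 512 control and 768 experimental.

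**1. The SAP's own error rates.** If a claim requires the lower limit of a two-sided interval of level C to exceed the margin, the error at the margin is (1−C)/2.

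- C = 0.95: (1−0.95)/2 = 0.025, and 1−0.975³ = 0.073. Both match the SAP.
- C = 0.975: 0.0125, and 1−0.9875³ = 0.037. Neither matches.
- C = 0.05: 0.475, and 1−0.525³ = 0.855. Neither matches.

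**2. The SAP's power table for Strategy 6 versus 3.** It assumes 6000 men and rTPF = 1. I take the conservative overlap to be the smallest possible, TPF_PSA + TPF_S3M − 1; this is my assumption. With N = 6000 × DR, the both-positive count is a = N(2·TPF−1)/TPF, and SE(log rTPF) = √[2(N−a)]/N. Power = Φ(−log 0.78/SE − z).

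- DR 0.015, TPF 0.57: N = 90, a = 22.1, SE = 0.1295. With z = 1.960, Φ(0.2485/0.1295 − 1.960) = 0.48. The SAP gives 0.48.
- DR 0.030, TPF 0.63: N = 180, a = 74.3, SE = 0.0808. Power 0.87. The SAP gives 0.87.

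All 16 entries agree within 0.01 at z = 1.960. With z = 2.241 (a 97.5% interval) the two corners become 0.37 and 0.80.

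**3. Power for Strategy 3 versus 1.** With 0.18 versus 1.3 × 0.18 = 0.234, SE = √(0.18×0.82/512 + 0.234×0.766/768) = 0.0228. Power at 95% is Φ(0.094/0.0228 − 1.960) = 98.4%, consistent with the stated figure of more than 90%. It would also exceed 90% at the other levels (97.0% at 97.5%), so this statement does not help to identify the intended level.

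**4. The levels as written, at α = 0.025.**

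| Place in SAP | Expression | Level | Multiplier | One-sided error at margin |
|---|---|---|---|---|
| Non-inferiority and superiority rules (ΔDP) | 2α×100 | 5% | 0.063 | 47.5% |
| Switching rule (ΔDP, rTPF) | 2(1−α)×100 | 195% | none | undefined |
| Interval formulas, both contrast sections | 100(1−α), z_{α/2} | 97.5% | 2.241 | 1.25% |
| Primary and key secondary endpoints | stated directly | 95% | 1.960 | 2.5% |

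**5. Finite-sample check.** Exact binomial enumeration of the Wald rule at 512 versus 768, with a true difference of −0.04:

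- Control rate 18%: 47.8% for the 5% interval, 2.7% for the 95% interval.
- Assumed control rates of 10% to 25%: 47.4% to 48.0% for the 5% interval, 3.0% to 2.7% for the 95% interval.

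**6. Scope.** The 2α rule is written for ΔDP only. The between-arm section assigns absolute differences to Strategies 3 vs 1, 2 vs 1 and 9 vs 7. Strategies 6 vs 1 and 5 vs 1 use relative differences, and the within-arm comparison 6 vs 3 uses rTPF. The relative-scale contrasts have correctly stated hypotheses and meet a wrong level only in the switching sentence and in the interval formulas.

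**The case against.** The strongest reply is that nobody could be misled. The hypotheses are stated correctly, p-values are one-sided, α is 0.025, 95% intervals are named under each endpoint heading, and the sample size note puts the error at 2.5% per test. A 195% interval cannot be computed, and no statistician would claim non-inferiority from an estimate minus 0.063 standard errors. This stands as an account of intent, and the power table supports it. It does not make the rule executable as written, and it does not dispose of the 97.5% formulas, which can be computed without any sign of trouble.

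A reader might infer more than the documents support:

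- **That the trial runs a 47.5% error rate.** It does not. That figure is the literal consequence of one formula which the rest of the SAP contradicts.
- **That the 5% rule governs every contrast, including the overarching primary comparison of Strategy 6 with 1.** It does not. That comparison is on the relative scale, for which no 2α interval is written.
- **That the direction is undefined, because an interval wholly below −δ also fails to cover it.** The alternative hypothesis and the switching rule, which requires the interval to lie above the margin, settle the direction. Clearer wording is still worthwhile.
- **That using δ for both margins is an error, because exp(−0.04) is not 0.78.** Each scale has its own margin: "We set the noninferiority delta to 4 percentage points" in the sample size assumptions, and δ = −log(0.78) in the updated calculation. They also agree at the 18% control rate: 1 − 0.04/0.18 = 0.778.

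**Conclusion.** The confidence levels in the claim rules are wrong as written and conflict with the SAP's endpoint sections and stated error rate. It is a notation error in the decision rule, and the intended level, 95%, can be recovered.

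The 47.5% figure assumes literal use of the 5% rule, with the lower limit required to exceed −δ, and concerns absolute-scale contrasts only. The more realistic risk is use of the 97.5% formulas. One-sided error would then be 1.25% instead of 2.5%, and power for Strategy 6 versus 3 would range from 0.37 to 0.80 instead of 0.48 to 0.87. Those lower figures rest on the smallest-overlap assumption, which reproduces the SAP's table.

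**What to change.** 1. In the section on non-inferiority and superiority tests, write two-sided (1−2α)×100% = 95% in the non-inferiority, superiority and switching rules.
2. State that the lower limit must be greater than −δ for non-inferiority and greater than θ for superiority.
3. Add the matching relative-scale rule: the lower limit of the 95% interval for rDP or rTPF must be greater than 0.78 for non-inferiority and greater than exp(θ) for superiority.
4. In both sections on contrasts, write 100(1−2α)% with z_α, so that a single α of 0.025 gives 95% intervals throughout.
5. Optionally, use separate symbols for the absolute margin (0.04) and the relative margin (−log 0.78 = 0.248).

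The cost is a dated textual clarification. If analyses have already been run, it should also record which interval level was used. Design, sample size, margins and data collection do not change.
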